### Analyses

We will evaluate for balance in baseline covariates between groups using *t* tests for continuous variables and Fisher’s exact test for categorical variables. Standardised differences between groups of 10 % or greater will be used as a threshold to signify clinically significant differences in baseline characteristics^(42)^. Our primary analyses will be a minimally adjusted intention-to-treat analysis wherein we will adjust for stratification factors (study site, adjuvant/neoadjuvant chemotherapy, and menopausal status)^(43)^. We will use generalised linear mixed models with a random effect for participant to account for individual variability. Time will be a repeated and fixed effect, with other fixed effects of group and group × time interaction. The distribution and link function that provides normally distributed residuals and/or the best model fit will be chosen for each outcome separately.

Planned secondary analyses include a per-protocol analysis (adherence to all aspects of intervention ≥ 5 of 7 d per week), a model with adjustment for covariates with clinically or statistically significant differences between groups at baseline, and a model with adjustment for covariates hypothesised to affect our outcomes including age and BMI.

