## Methods

### Study design, randomisation and blinding

IMPACT-Women is a two-site, two-arm, parallel-group superiority randomised controlled trial. Participants will be randomised 1:1 to the two groups using permutated blocks with random block sizes of two and four, stratified by study site, chemotherapy type (adjuvant/neoadjuvant), and postmenopausal status (yes/no). Randomisation will occur after completion of baseline assessments using a blinded online electronic randomisation tool, with enrolment and assignment performed by a research coordinator. All outcome assessors will be blinded to group assignment. Blinding participants to a behavioural intervention is not possible but is not expected to bias our physiological outcomes. Participants’ treating oncologists will not be blinded as we expect that group assignment may need to be discussed during care.

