### Sample size

The proposed sample size of *n=*130 was calculated using the primary outcome of visceral AT at the end of chemotherapy on GLIMMPSE software (https://glimmpse.samplesizeshop.org/). To calculate sample size, we used the average visceral AT change and its correlation between time points generated by our TRE pilot study (–4·8%) using identical MRI methods. For the comparison group, we used an average change of +6·6 % which we previously observed during 12 weeks of chemotherapy in a similar patient group at one of the included institutions^(40)^. For the time correlation matrix, we used the correlations between time points observed in our pilot data (*r* = 0·9866). However, to allow for an expected increase in variability induced by chemotherapy, we estimated a 25 % increase in variability (1·25 scale factor for covariance matrix) and standard deviation at the end of chemotherapy. Using the above values, *n=*116 total participants would provide 90 % power to detect a group × time interaction with *P* ≤ 0·05 for the Hotelling–Lawley trace test (which most closely approximates mixed models). We estimate a 12 % total loss to follow-up based on rates reported for TRE studies (∼10 %)^(41)^ plus 2 % for technical difficulties. Therefore, we will recruit *n*=130 total participants (*n*=65 per group).

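### With 65 per arm, the 10 % standardised-difference rule would flag about 57 % of unstratified baseline covariates by chance, and those flags then choose the covariates of a planned secondary model

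*Protocol article*

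**What the plan says.** All the relevant rules stand in the Analyses section of the protocol article.

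- **Baseline tests.** The section says "We will evaluate for balance in baseline covariates between groups using" t tests for continuous and Fisher's exact test for categorical variables. It gives no significance level for this check.
- **Threshold.** "Standardised differences between groups of 10 % or greater will be used as a threshold to signify clinically significant differences in baseline characteristics".
- **Use of the flags.** The planned secondary analyses include "a model with adjustment for covariates with clinically or statistically significant differences between groups at baseline". Because of the word *or*, the 10 % rule alone is enough to admit a covariate.
- **Primary analysis.** "Our primary analyses will be a minimally adjusted intention-to-treat analysis wherein we will adjust for stratification factors", that is, study site, adjuvant or neoadjuvant chemotherapy, and menopausal status.
- **A separate prognostic model.** A further secondary model adjusts for covariates expected to affect the outcomes, with age and BMI given as examples.

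The Study design section describes the allocation: "Participants will be randomised 1:1 to the two groups using permutated blocks with random block sizes of two and four", stratified by the same three factors. The Sample size section gives 65 participants per group.

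**The concern.** A fixed cut-off of 0.10 takes no account of how much two randomised groups of 65 differ by chance. If that chance spread is wide compared with 0.10, the rule mostly picks up noise and reports it as clinically meaningful. The same 0.10 applies to every variable, so the label carries no clinical content for any of them.

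The t and Fisher tests have a related weakness. When allocation is properly random, the null hypothesis they test is true by design, so a small P value tells the reader nothing about which covariates matter.

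Both criteria then choose an adjustment set. Covariates enter because they happened to differ between arms, not because they predict visceral fat. Readers may take that model as a robustness check on the main result, although its content is settled by chance.

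**Working it through.** **Inputs.** 65 per group (Sample size); 1:1 allocation (Study design); threshold 0.10 (Analyses).

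**The plan's own figure.** The Sample size section says "116 total participants would provide 90 % power to detect a group × time interaction" and allows 12 % loss. 116 × 1.12 = 129.9, which gives 130, or 65 per arm, as stated. Dividing instead gives 116 / 0.88 = 131.8, or 132. The two differ by 2 participants, which does not matter here. The 116 itself cannot be rebuilt because the standard deviation is not given, but nothing below depends on it.

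**Chance spread.** For a covariate not controlled by stratification, the standardised difference *d* is approximately normal with mean 0 and variance 2/n.

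- Standard error = √(2/65) = 0.1754.
- 0.10 / 0.1754 = 0.570 standard errors.
- P(|d| ≥ 0.10) = 2 × [1 − Φ(0.570)] = 0.569. With the t distribution on 128 degrees of freedom it is 0.570.

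**Checks on that result.**

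| Case | Chance of a flag |
|---|---|
| Continuous covariate, 65 per arm | 0.57 |
| Binary covariate, 65 per arm, exact, prevalences from 5 % to 50 % | 0.53 to 0.59 |
| Continuous covariate, 58 per arm (116 in total) | 0.59 |
| Continuous covariate, 10,000 simulated trials with stratified blocks of two and four | 0.56 |
| Each stratification factor, same simulation, equal-sized strata assumed | below 0.01 |

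**Number of flags.** The article gives no covariate list, so the counts here are assumptions, with covariates taken as independent.

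- 5 covariates: P(at least one flag) = 1 − (1 − 0.569)^5 = 0.985.
- 10 covariates: 10 × 0.569 = 5.7 expected flags.
- 20 covariates: 20 × 0.569 = 11.4 expected flags.

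**The two criteria compared.** Taking 0.05 as the level of the baseline tests (an assumption), a t test reaches it at |d| = 1.979 × 0.1754 = 0.347. A difference of exactly 0.10 has P of about 0.57. For continuous covariates, then, every significant variable has already been flagged by the 10 % rule, and the tests add nothing to the selection.

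**Scale.** A chance flag rate of 50 % would need 2 × (0.6745/0.10)² = 91 per arm. A rate of 5 % would need 2 × (1.96/0.10)² = 768 per arm.

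**What the flags do to the estimates.** Assume a linear model with a participant random intercept and baseline covariates as main effects.

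- *Group × time.* With complete data this is a difference between groups in mean change. A covariate that is constant within a participant cancels from the change, so the estimate does not move.
- *Group difference at the end of chemotherapy.* This is the group term plus the interaction. The group term shifts by the sum, over covariates, of each coefficient times its between-group difference. It therefore does depend on which covariates were flagged.

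**The case against.** The strongest reply is that nothing important depends on this model. The primary analysis is fixed in advance and adjusts only for the stratification factors. The sample size is based on the group × time interaction, which the extra covariates leave unchanged with complete data. In a simulation of 130 participants with 11 added covariates and 12 % missing at follow-up, the largest change in 40 runs was 0.0012 against a standard error of 0.032. This stands, under an identity link and without covariate × time terms, neither of which the article settles. A reader might infer that the trial's main result is at risk; the document does not support that. The reply does not cover the group difference at the end of chemotherapy, the time point at which the Outcomes section defines the primary outcome, and it leaves the false labels in place.

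A second reply is that a standardised difference describes the size of an imbalance and should not be judged by a test's error rate. That is fair for a descriptive use. Here, however, the plan turns it into a decision rule with an interpretation attached. The 768 per arm is only a gauge of scale. The plan cites a source for the threshold, which cannot be examined here, and the calculation does not depend on it.

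Two stronger readings should be set aside. One is that all baseline covariates are exposed: the three stratification factors are nearly balanced by design. The other is that the covariate set must stay unknown until unblinding. The article blinds outcome assessors, describes no blinding of analysts, and places baseline assessments before randomisation, so imbalance could be examined before any outcome is seen. That would still not make the selection prognostic.

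**Conclusion.** The point holds for covariates other than site, chemotherapy timing and menopausal status. Each has about a 57 % chance of being declared clinically significant through randomisation alone. The figure rests on two stated inputs, 65 per arm and the 0.10 threshold. It is an expectation: baseline variables are correlated, so the share seen in the trial will vary around it.

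The consequence is limited to misleading baseline statements and a data-driven secondary model. This should be corrected, but it does not threaten the primary analysis. Nor is it a matter of detail left to a fuller document, because the article itself fixes the threshold, its meaning and its use.

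**What to change.** Delete three things from the Analyses section: the baseline significance tests, the 10 % rule with its label, and the imbalance-driven model. Report baseline values by group descriptively; standardised differences may be shown, without a threshold.

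Keep the secondary model with prognostic covariates that is already planned, and close its list before outcomes are compared: the stratification factors, age and BMI, with any others named in advance. Do not enter baseline visceral fat as a covariate where it is already a response in the repeated-measures model, because that puts the same measurement on both sides. Baseline should be handled one way only.

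The cost is a few deleted sentences and one fewer model. Readers used to baseline P values, or to a sensitivity model adjusted for observed imbalance, will not see them.

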### Data management

Data will be de-identified using a studyID and will be securely stored with access limited to study staff and investigators. Electronic data entry or extraction will be double-checked for accuracy.

## Discussion

Metabolic toxicity is an important emerging side effect from chemotherapy treatment resulting in rapid onset of metabolic dysfunction and persistent impairments after treatment completion^(8,10,11)^. This trial will examine the impact of a novel multimodal metabolic health intervention to attenuate changes to metabolic impairments including ectopic AT deposition and CVD risk. To our knowledge, no previous trials have implemented TRE or interventions to reduce sedentary time during active cancer treatment. Given that the causal independence of physical activity from diet is not well established, we chose to combine these two interventions which both show promise as feasible, safe and effective metabolic health interventions that could be easily scaled for implementation within clinical practice. The final component of our multimodal intervention focusses on improving healthy eating practices through nutritional education and counselling. Diet plays an obvious role in energy and protein intake and therefore energy and protein balance and ultimately cardiometabolic health^(44)^. A registered dietitian-led nutrition education and counselling intervention also provides an opportunity to aim to limit the spontaneous 20–30 % calorie restriction that typically occurs with *ad libitum* 16:8 TRE and to provide guidance on ensuring adequate protein intake in line with oncology guidelines^(28)^.

Our intervention is designed to address potential barriers to adherence common among patients receiving active cancer treatment. For example, we incorporated guidelines that allow participants to deviate from strict TRE in ways that are still supported by evidence for cardiometabolic health effects, including altering the length of TRE, selecting the start time of their eating window and guidance for taking a day off from TRE when required. Accounting for personal preferences in health interventions has been found to enhance recruitment and foster participant autonomy, enjoyment, and intervention adherence^(45,46)^. To overcome the common barrier of added study visits on top of extensive medical appointments, the intervention is delivered by phone, and in-person outcome assessments are only required three times over 2 years. This remote delivery format also increases potential for widespread implementation and future scalability to health systems and more remote communities. We will disseminate study results through academic conferences, peer-reviewed publications, and targeted patient and clinician events (e.g. survivorship groups and Grand Rounds).

A strength of this study is the use of 3T MRI as a non-invasive, safe (no ionising radiation), and highly reproducible technique to quantify the primary outcome (visceral AT), and other ectopic AT pools in the liver and thigh muscles. Our study will provide novel additions to the emerging evidence that rapid expansion of ectopic AT pools and their associated metabolic and/or cardiovascular dysfunction during breast cancer treatment plays a central role in the increased risk of CVD events among breast cancer survivors.

We have taken steps to minimise potential sources of bias. While blinding participants and their care team is not possible due to behavioural nature of the intervention and for patient safety, all outcome assessors will be blinded to the group assignment. In addition, participants in the comparison group will receive the same number and timing of calls to control for social impact and to assess contamination. One limitation is that we are using a parallel study design to implement a multimodal intervention which limits our ability to determine the individual effects of each component of the intervention.

In summary, the IMPACT-women study will evaluate the short- and longer-term effects of a multimodal metabolic health intervention during chemotherapy treatment for early-stage breast cancer on markers of metabolic health at the end of chemotherapy. The phone-based intervention consists of *ad libitum* TRE, healthy eating, and reducing sedentary time compared to usual cancer and supportive care. By attenuating the effect of chemotherapy on visceral AT accumulation and cardiometabolic dysfunction, our intervention has the potential to reduce risk of cardiometabolic disease and related mortality among breast cancer survivors.
